## Abstract

Data concerning the combined effect of diet and exercise interventions on overall health in the elderly are scarce. The MED-E project’s primary aim is to assess the effect of the different 3-month sustainable healthy diet (SHD) and multicomponent training (MT) interventions on several health outcomes in the elderly. A quasi-experimental study assigned older adults into four groups: (1) SHD, (2) MT, (3) SHD + MT, or (4) control group (CG). The SHD intervention included a weekly offer of a mixed food supply and individual and group nutritional sessions on the principles of an SHD. The MT groups were submitted to 50-min exercise sessions three times a week. The primary outcomes were blood biomarkers and metabolic profile alterations that were assessed pre- and post-intervention. Additionally, data on dietary intake and nutritional adequacy, physical fitness, body composition and anthropometry, cognitive function, quality of life, and geographical data were assessed at the same time points. The MED-E project’s study protocol and future results will add to knowledge about the importance and beneficial contribution of combined SHD and MT interventions on healthy ageing policies.

## 1. Introduction

Population ageing is a concerning demographic phenomenon which is accompanied by a greater prevalence of chronic diseases. This disease burden increases healthcare costs and compromises individuals’ global health status. The adoption of lifestyle risk behaviours such as inadequate diets or under-activity may be a major contributor to poorer health statuses [1]. Studies report that unintentional nutritional and functional changes are more frequent in individuals aged 65 years or older [2,3].

Older adults have a dietary intake below recommendations in several nutrients: protein, n–3 fatty acids, dietary fibre, carotenoids, calcium, potassium, selenium, and vitamins B6, B12, D, and E [4]. It is also known that overconsuming saturated fat and sodium [4] is expected. The Mediterranean Diet [5] and the Dietary Approaches to Stop Hypertension (DASH) [6] are the most studied healthy dietary patterns, with more evidence regarding positive health benefits. These are characterised by high consumption of plant-based foods, e.g., vegetables, fruits, whole grains, and pulses, and low consumption of sweetened foods, refined grains, and processed meat [6]. Healthy, nutritionally balanced, and low environmental impact diets have been gaining awareness to improve population and planetary health [7,8]. Sustainable healthy diets (SHD) that are richer in plant-based and poorer in animal-based foods—such as the adapted Mediterranean Diet [5,9,10,11]—have been associated with nutritional adequacy; reduced body fat; decreased risk of weight gain, overweight, or obesity [8,12]; reduced frailty [13]; and better mental health [14]. Healthy dietary patterns improve lipidic (lowering triglycerides, total cholesterol, and low-density lipoprotein cholesterol—LDL-C) and inflammatory profiles, being associated with a reduction in C-reactive proteins (CRP), plasminogen activator inhibitor-1 (PAI-1), tumour necrosis factor-alpha (TNF-α), interleukin 6 (IL-6), and leptin [15,16].

Since older adults spend an average of 9.4 h/day engaged in a sedentary behaviours, which corresponds to 65–80% of their waking time [17], and are the least physically active segment of the population, engagement in physical activity (PA) routines should be considered in this age group. Exercise benefits to functional and cognitive capacities are well demonstrated in the literature [18], in addition to improvements in glycaemic control [19], inflammation [20], and body fat reduction [21]. Sampaio et al. (2019) demonstrated that regular multicomponent training (MT) sessions diminish the physiological effects of sedentary routines by improving quality of life, mobility, balance control, and bone mineral content [20], thereby delaying the development and progression of chronic and disabling conditions. Most studies regarding the impact of exercise on biomarker profiles were developed with different types of training (strength or aerobic programs). The literature shows a decrease in LDL-C, total cholesterol, CRP, IL-6, TNF-α, leptin, glycosylated haemoglobin A1c (HbA1C), insulin, and glucose, and an increase in high-density lipoprotein cholesterol (HDL-C) [22,23]. In MT programs, studies have corroborated previous findings concerning improving lipid profiles—lowering triglycerides and elevating HDL-C—and antioxidant capacity [24].

Moreover, studies regarding the combined effect of sustainable healthy dietary patterns and exercise interventions are scarce. The few existing studies suggest an intensification of the effects of isolated interventions with other beneficial health outcomes [25]. Besides the classical and standard biochemical analyses, untargeted nuclear magnetic resonance (NMR) spectroscopy-based metabolomics have begun to gain insight. This technique allows for the semi-quantification and analysis of hundreds of low molecular weight metabolites in biofluids, stools, and tissues [26,27], enabling the routine identification of novel compounds. Existing studies of diet and exercise approaches are based on short-term duration and strictly controlled and isolated diet or exercise intervention protocols, mostly with different population groups (such as children or younger adults) [28]. More extended intervention studies conducted under less strict diet and exercise programs are sparser. The qualitative and quantitative differences in metabolic profiles resulting from this combined intervention in the elderly have not yet been explored.

According to the socio-ecological model, an individual’s behaviour is affected by and affects the social environment. Therefore, holistic interventions are more practical in addressing healthy ageing [29]. Environmental factors may have an essential role in the modulation of food and physical activity (PA) habits [30]. Food, such as availability and accessibility to supermarkets, grocery or convenience food stores, and restaurants [30], and PA, such as details on walkability, parkland use, access to PA facilities [30,31], and environmental features must be considered. The use of Geographic Information Systems (GIS) can provide a novel and better understanding of the available environmental features, contributing to the implementation of effective healthy ageing policies [29].

Therefore, our primary aim is to assess the effect of different SHD and MT interventions on the biochemical and metabolic profiles, nutritional statuses and adequacy, physical fitness, body composition and anthropometry, cognitive function, and quality of life of older adults through a quasi-experimental study. Additionally, as a secondary aim, we intend to characterise food and PA environmental features and study their potential role in the modulation of food and PA practices.

## 2. Design and Methods

The study was designed as a quasi-experimental, 12-week, four-armed, diet and exercise intervention with community-dwelling elderly residents from Porto, Portugal (Figure 1). This protocol report follows the Standard Protocol Items: Recommendations for Interventional Studies (SPIRIT) 2013 checklist [32]. 

### 2.1. Participant Involvement and Study Design

This multicentre quasi-experimental study was conducted in the Porto metropolitan area, Portugal. Participants were recruited from community programs, daycare centres, municipalities, healthcare centres, and social media platforms through phone calls, informative flyers, and presential and online meetings. Additionally, a short presential session was provided to motivate participation and clarify doubts about the program. Data collection started in November 2021 and ended in December 2022.

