#### 2.6.3. Confounders

As possible confounders, we will control at baseline and after the intervention for (i) sociodemographic and economic status, (ii) clinical history, (iii) tobacco use, (iv) medication (collected through a structured questionnaire), and (v) daily physical activity, assessed through an accelerometry-based method (ActiGraph GT9X Link, Manufacturing Technology, Inc., South Bend, IN, USA). Participants were instructed to always wear the accelerometer for seven consecutive days attached to an elastic belt, except when sleeping or during water activities. Data were collected in 100 Hz epochs; valid data must include a minimum of 10 h on at least four days (with one weekend day). This data will be processed using Actilife™ software, version v6.13.4 (Actigraph LLC, Pensacola, FL, USA) and organised as sedentary, light, moderate, and vigorous physical activity.

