## 3. Discussions

We expect to disseminate study results by publishing manuscripts in peer-reviewed scientific journals and giving presentations at national and international conferences. Additionally, we will promote seminars for the entire community, particularly for the participants and healthcare organisations, and disseminate essential results through institutional public media (webpage, social media networks). Participants will be informed individually of their study results by synthesised reports.

This study describes the protocol of a quasi-experimental study of 3-month SHD and MT interventions for older adults comprehended on the MED-E project. 

Some innovative aspects of this study should be underlined. Data were obtained from an urban population of a high-income South European country living in Porto, mostly from Paranhos (same parish), with similar baseline conditions regarding physical activity and sociodemographic and economic conditions, which empowers the study. Most outcome variables were objectively assessed, reducing the risk of measurement or misclassification errors. Additionally, having the same intervention location for all participants will minimise bias. Moreover, this project followed the latest recommendations for diet and exercise interventions for this population group. Using cutting-edge technologies, specifically NMR-based metabolomics, we aim to determine how diet and exercise can impact several biomarkers and metabolites. Compared to most studies on the impact of nutritional and dietary interventions on health, this study includes an SHD food intervention. It also has a more extended intervention period than is usually observed. It has a practical component, promoting the direct involvement of participants in the SHD culinary workshop. Additionally, continued, individually adjusted, and personalised MT sessions may positively impact the functionality and cognitive capacity of older adults and improve their quality of life. Our findings will provide needed insights and help to strengthen the current evidence regarding nutrition and exercise as complementary adjuvant approaches to promoting healthy and active ageing.

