Some challenges to this study must be recognised. Firstly, we anticipate a potential sample with several age-related comorbidities. Secondly, the elderly tend to mainly adopt sedentary behaviours, increasing difficulties in the recruitment process. Based on differences in baseline participant characteristics, a misinterpretation of the primary outcomes and an inability to generalise the results may occur. Considering the main inclusion criteria, the different interventions cannot be generalised to other specific populations. Despite including participants with lower nutritional status or who were inactive, we cannot exclude the possibility that the participants involved in the study were more prone to healthy lifestyle behaviours. Though, this bias was minimised by excluding participants that were engaged in regular physical activity or consulting a nutritionist. Additional research will help identify the most effective diet and exercise intervention protocols for more heterogeneous, non-uniform, and other specific population groups. A cross-over and randomised controlled trial (RCT) design, where the same participant implemented different interventions, would reduce the likelihood of heterogeneity affecting the evaluation of primary outcomes. Initially, our study protocol was thought and designed to be a cross-over RCT. Although, the methodology needed to be adapted due to the beginning of the unpredictable pandemic situation, which occurred simultaneously with the start of the recruitment study and disabled the sample randomisation. The pandemic situation delayed and imposed logistical difficulties in the recruitment process. The lockdown and isolation of this at-risk population group (older adults) affected baseline assessments and the study intervention due to the closure of facilities.

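### Calendar time is missing from the stated confounders, although the arms were not randomised, data collection spanned up to 14 calendar months, and the article does not say whether the arms ran concurrently

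*Protocol article*

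**What the plan says.** Section 2 gives the design: "The study was designed as a quasi-experimental, 12-week, four-armed, diet and exercise intervention". Section 2.2 has one assessment at baseline and one after three months of intervention, and gives no allocation rule. The Discussion (section 3) says that a randomised cross-over was first intended and was given up because of the pandemic, "which occurred simultaneously with the start of the recruitment study and disabled the sample randomisation".

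On timing, section 2.1 says "Data collection started in November 2021 and ended in December 2022". The Discussion adds that lockdown and isolation "affected baseline assessments and the study intervention due to the closure of facilities". Section 2.5.2 describes a two-month adaptation period before the training programme; no such lead-in is described for the diet-only or control arm.

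On adjustment, section 2.6.3 numbers the possible confounders: "i) sociodemographic and economic status, (ii) clinical history, (iii) tobacco use, (iv) medication", and fifth, daily physical activity by accelerometry. Section 2.7 says covariates were chosen a priori, gives examples from the same set, and keeps only those that change the association by at least 10%. The effect test is the repeated-measures analysis with its interaction.

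On place, section 2.1 says "This multicentre quasi-experimental study was conducted in the Porto metropolitan area", and section 2.5.2 puts the training in gymnasiums, in the plural. The Discussion counts as a strength that "having the same intervention location for all participants will minimise bias".

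**The concern.** With one measurement on each side of a 12-week intervention, each participant's change carries whatever the calendar did over those weeks. The article itself treats diet as seasonal: the SHD sessions present the seasonal foods of each month, and the Food Propensity Questionnaire asks about seasonal intake. Randomisation within a common recruitment period would have spread this drift evenly over the arms. Here there is none, and nothing states that the arms ran side by side.

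An arm observed from winter to spring and another from summer to autumn would drift differently without any intervention effect. That difference is a group-by-time interaction, the quantity that section 2.7 tests. Adjusting for sociodemographic factors, clinical history, tobacco or medication cannot remove it. Daily physical activity may carry some seasonal signal, but it is also measured after the intervention and training may alter it, so it cannot stand in for calendar time.

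**Working it through.** The article gives no figure for seasonal drift, so there is none to reproduce. Its design figures supply the inputs.

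**Inputs from the article.** Window: November 2021 to December 2022, up to 14 calendar months (2.1). Intervention: 12 weeks = 84 days (2). Planned 25 per group with 20% dropout (2.3), so 25 × 0.80 = 20 completers per arm, 80 in total.

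**Assumed inputs.** The size of any seasonal effect is not in the documents. I use an amplitude A of 0.10 to 0.25 SD of the marker, and separately a two-season effect s of 0.2 to 0.5 SD of the change score.

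**1. Room for staggered starts.** One concurrent wave needs about 3 months, or about 5 with the two-month adaptation. The window is far longer, so staggered starts are possible. The window dates data collection, not intervention delivery, so it does not prove them.

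**2. Upper bound.** Let the marker follow y(t) = A·sin(2πt/365). The change over 84 days is

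y(t+84) − y(t) = 2A·sin(π·84/365)·cos(2π(t+42)/365).

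Since sin(π·84/365) = 0.662, the largest change is 2 × 0.662 × A = 1.32A. Two arms half a year apart have opposite signs, so they differ by at most 2.65A. A = 0.10 SD gives 0.26 SD; A = 0.25 SD gives 0.66 SD. Concurrent arms differ by zero. For a fixed interval, the drift is a combination of a sine and a cosine of the baseline date, so those two terms would absorb it.

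**3. A milder illustration.** Suppose there are two seasons, and two arms differ by p in the share of participants seen in one of them. The bias is b = s·p. With no intervention effect, the rejection probability at nominal 0.05 follows from a noncentral t with 38 degrees of freedom and noncentrality b/√(2/20).

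| s (SD of change) | p = 0.5: bias, rejection | p = 1: bias, rejection |
|---|---|---|
| 0.2 | 0.10, 0.061 | 0.20, 0.095 |
| 0.3 | 0.15, 0.075 | 0.30, 0.152 |
| 0.5 | 0.25, 0.120 | 0.50, 0.338 |

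For the four-arm test with N = 80 and both training arms shifted together by 0.2, 0.3 or 0.5 SD, rejection is 0.099, 0.169 or 0.420 (noncentral F, f = half the shift).

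**4. Cost of adjusting.** With f = 0.40 (the stated effect size read as Cohen's f) and 80 completers, power is 0.845 with one covariate and 0.844 with four or five, so degrees of freedom hardly matter. Collinearity does. With the two seasons split evenly overall, the variance of an arm contrast is multiplied by 1/(1 − p²):

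- p = 0.25: 1.07
- p = 0.50: 1/(1 − 0.25) = 1.33
- p = 0.75: 1/(1 − 0.5625) = 2.29
- p = 1: the contrast cannot be estimated.

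**5. Place.** Multicentre (2.1) and gymnasiums (2.5.2) point to several sites. The Discussion's single location, and section 2.5.1's one faculty kitchen for the workshop, point to one. The article gives no number of centres and does not say whether multicentre refers to recruitment or to delivery.

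**The case against.** The strongest reply is that this is an omission from a condensed article. Section 2.7 introduces its covariates as examples, section 2.6.3 calls its items possible confounders, and an analysis plan could add a wave term. That carries some weight, but the article does more than stay silent. It numbers a list, says the covariates were fixed a priori, and sets a retention rule that works only on that set. Applied as written, calendar time is never tested.

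The second reply is that no passage shows the arms differing in timing. That stands. Section 2.2 mentions two assessment periods, which could mean periods common to all arms. The closures are not dated, and nothing says they hit the arms unequally. A reader might infer that season or closures have already biased the comparison; the article does not support that.

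A reader might also infer confounding by site. That is not established either: the Discussion claims a single intervention location and participants mostly from one parish, and multicentre may describe the recruitment sources listed directly after it. What remains is a contradiction to resolve.

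Third, 2.65A is a worst case. It needs a purely sinusoidal marker, whole arms starting together, starts half a year apart, and both arms centred on the steepest slopes. No marker in the panel is shown to behave so. This stands, and the figure is used only as an upper bound.

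Finally, the Discussion already warns that baseline differences could lead to misinterpretation of the primary outcomes. That is a general caution and does not adjust for period.

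**Conclusion.** The point holds as a conditional weakness in the stated adjustment set. The arms are non-randomised, the window is long enough for staggered starts, closures are acknowledged, and calendar time is not among the a priori confounders. Whether bias follows depends on a fact that the article does not give: whether the arms ran concurrently.

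If they did, the bias is zero. If they did not, it is bounded by 2.65A for a sinusoidal marker, or 0.26 to 0.66 SD at the assumed amplitudes. This takes the same 84-day interval in every arm. Closure-related drift is not periodic and lies outside this bound. At a 50-point imbalance between two seasons, the rejection probability with no intervention effect is 0.061 to 0.120 instead of 0.05, under assumed effects of 0.2 to 0.5 SD.

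On place, the finding is limited to the conflict between the multicentre description and the single-location claim.

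**What to change.** 1. In 2.6.3 and 2.7, add calendar time of the baseline visit, as sine and cosine of month or as enrolment wave. Keep it in every outcome model, outside the 10% rule, and let it act on the change (a time-by-covariate term in the repeated-measures model). Wave is the better choice if closures are the main worry, because they are not periodic.
2. Tabulate start month by arm and state whether the arms ran concurrently. Say also where the adaptation period falls relative to the baseline assessment.
3. Where two arms share no calendar period, state that period and intervention cannot be separated for that comparison. Data collection has ended, so no covariate can recover it.
4. Reconcile 2.1 and 2.5.2 with the Discussion on location. If there was more than one intervention site, add centre as a covariate and drop the claim that a common location minimises bias.

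The cost is one table and a few degrees of freedom; the exact number depends on the number of waves and centres, which the article does not give. Visit dates are needed, and the article does not say how they are held. Intervals widen little if the arms overlap well in time. They widen materially if not: variance rises by a factor of about 1.33 at a 50-point and 2.29 at a 75-point difference in seasonal share.

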### 2.2. Eligibility and Recruitment

This study included individuals (i) aged 65 years or older, (ii) living in the community, (iii) with independent mobility, (iv) with no past medical history of neuropsychiatric conditions (e.g., major depression or bipolar disease), and (v) with no musculoskeletal or cardiovascular disorders that contraindicate participation in moderate exercise and testing. The exclusion criteria included individuals engaged in regular moderate to vigorous exercise training and followed by a nutritionist.

Eligible participants received a complete explanation of the study’s purposes, risks, and procedures. Before data collection, the principal researcher obtained informed consent from interested participants. After the agreement, participants were assigned into a 3-month SHD, MT, combined SHD and MT (SHD + MT), or control group (CG). 

Participants were assessed at baseline and after 3 months of intervention. At baseline, sociodemographic and economic, lifestyle (e.g., tobacco use and habitual physical activity), and general clinical data were collected through a structured questionnaire. Possible changes in these data were assessed in post-intervention assessments. At these two time points, nutritional and food intake evaluations were obtained through multiple reliable tools [33,34,35]: the Mini Nutritional Assessment [36]; physical capacity assessments through the Senior Fitness Test [37] and handgrip strength; a whole-body Dual X-ray absorptiometry (QDR 4500/A, Hologic Explorer, version 12.4, Bedford, MA, USA); a Montreal Cognitive Assessment [38]; the Quality of Life for Old Module (WHOQOL-OLD) [39]; and accelerometry (ActiGraph GT9X Link, Manufacturing Technology, Inc., South Bend, IN, USA) were performed. 

Participants were only informed about which group they belonged to after baseline assessments. Well-trained and skilled researchers executed the same procedures during the two assessment periods.

